#### Statistical Methods

Demographic characteristics (age, sex, residency semester), having the national diploma in echocardiography, number of TTE performed, number of TEE observed, desire for a technical specialty in Cardiology collected at the time of randomization, will be summarized and compared between participants of the “traditional group” and the “simulation group.” Continuous data will be reported as means ± standard deviation (SD) for normally distributed data or as medians and interquartile range (IQR) for non-normally distributed data, as assessed through graphical methods and the use of the Shapiro-Wilk test for normality. Categorical data will be reported as counts and percentages. Between-groups comparisons will be performed using Student's *t*-test or Mann–Whitney test for continuous variables and using the Chi-2 or Fisher's exact test for categorical variables, as appropriate. Regarding the co-primary outcomes, on-parametric approaches (i.e., Mann-Whitney tests) will be favored over parametric tests due to the skewed distribution of test scores previously described in the literature (15). For within-groups comparisons (pre- vs. final tests), paired *t*-tests and Wilcoxon signed-rank tests will be performed for continuous variables. Longitudinal analysis of the evolution of the co-primary outcomes over the two time points (pre- and 3-month follow-up) will rely on mixed effects linear regression modeling, accounting for the correlation between repeated data over time. To address this risk of bias due the difference of number of TEE observed between the residents, an adjustment for the number of TEE observed will be performed in the final analysis. Prespecified subgroup analyses will be performed after stratifying by prior experience of video games in childhood or currently. A two-tailed *p* < 0.025 will be considered statistically significant for the primary analyses, and a two-tailed *p* < 0.05 for all other comparisons. All data will be analyzed using the *R* software, version 3.6.3 (R Project for Statistical Computing, R Foundation, Vienna, Austria) and Stata v16.0 (StataCorp, College Station, TX, USA).

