### Randomization

Randomization with stratification by center will be performed at the individual (resident) level in 1:1 ratio, using a computer-based software (Research Randomizer 4.0; Social Psychology Network, Middletown, USA) to assign all the residents to the traditional group or to the simulation group. The random allocation sequence will be computer-generated by the statistician ([name]) prior to the study using Stata v16.0 (StataCorp, College Station, TX, USA). Cluster-level randomization at the center level was not used for the present study, considering as minimal the risk of “contamination” of the effect of the training intervention in residents allocated in the control group.

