### Baseline Participants Characteristics

The following demographic data will be collected: age, sex, residency semester, having the national diploma in echocardiography (validation on the SIDES platform), number of TTE performed, number of TEE observed, desire for a technical specialty in cardiology (cardiovascular imaging, interventional cardiology, electrophysiology, pediatric and congenital cardiology, or no technical specialty). All participants will answer a questionnaire on their prior experience of video games in childhood or currently, defined by more than 1 hour per week, as this seemed to be associated with performance on simulation-based models in previous studies (15, 24).

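### Baseline variables are significance-tested between randomised arms, while the adjusted analysis names only one covariate and leaves out other baseline variables that are collected and plausibly prognostic

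*Protocol article*

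**What the plan says.** In the Protocol article, Baseline Participants Characteristics lists what is collected at entry, including "residency semester, having the national diploma in echocardiography (validation on the SIDES platform), number of TTE performed" and the number of TEE observed.

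Statistical Methods takes up seven of these variables: age, sex, residency semester, and then "having the national diploma in echocardiography, number of TTE performed, number of TEE observed, desire for a technical specialty in Cardiology". It says that these data, "collected at the time of randomization, will be summarized and compared between participants of the" two groups. The tests follow: "Between-groups comparisons will be performed using Student's *t*-test or Mann–Whitney test for continuous variables", with chi-squared or Fisher tests for categorical variables. The threshold is 0.025 for the primary analyses and "a two-tailed *p* < 0.05 for all other comparisons".

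On the outcome side, non-parametric tests are preferred for the co-primary scores ("i.e., Mann-Whitney tests) will be favored over parametric tests due to the skewed distribution of test scores"). A mixed linear model covers the pre-test and 3-month scores. On covariates there is one statement: "an adjustment for the number of TEE observed will be performed in the final analysis".

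The Randomization section states that "Randomization with stratification by center will be performed at the individual (resident) level in 1:1 ratio".

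**The concern.** Two linked points arise.

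First, under individual randomisation the null hypothesis of a baseline test is true by design. A significant result then reflects only chance. It says nothing about whether the difference matters for the outcome, which depends on how strongly the variable predicts the score. In print, such a result can cast doubt on a sound randomisation.

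Second, the variables tested in this way would be more useful as covariates. All four residency years are eligible, with or without the echocardiography diploma, so semester, diploma and TTE count plausibly predict the scores. None is named in any model. The one covariate that is named is ambiguous: the number of TEE observed is collected at baseline, and the section on training also has residents log TEE observed or performed after training. Statistical Methods does not say which count is meant.

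At stake are a misleading baseline table and some precision in the adjusted estimate. The validity of the trial is not in question here.

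**Working it through.** **1. The plan's own figure.** Inputs from Sample Size Calculation and Statistical Methods: difference 5 points, SD 7, two-sided alpha 0.025, power 90%.

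- Normal formula: n per group = 2 × 7² × (2.241 + 1.282)² / 5² = 48.7, so 49.
- t-test (noncentral t): power 0.894 at 49 and 0.900 at 50 per group.

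The stated 50 per group reproduces.

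**2. Chance of a false baseline flag.** With k independent tests at 0.05 and randomisation intact, the chance of at least one p < 0.05 is 1 − 0.95^k.

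- All seven listed variables: 1 − 0.95^7 = 0.302, with 7 × 0.05 = 0.35 false positives expected.
- Semester, diploma and TTE count alone: 1 − 0.95^3 = 0.143.

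Age, semester, diploma, TTE count and TEE observed probably all rise with time in training. In a simulation with an assumed pairwise correlation of 0.5 to 0.7 among the test statistics of those five, and independence for the other two, the chance for all seven is 26% to 23%. So 30% is an upper figure.

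**3. What more covariates could buy.** The documents give no R², so a range is assumed for the share of variance explained beyond what the analysis already removes. Residual SD = 7 × √(1 − R²), with 50 per group, difference 5 and two-sided alpha 0.025 (t-test):

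| Extra R² (assumed) | Residual SD | Fall in standard error | Power |
|---|---|---|---|
| 0 | 7.00 | 0% | 90.0% |
| 0.05 | 6.82 | 2.5% | 91.6% |
| 0.10 | 6.64 | 5% | 93.0% |
| 0.20 | 6.26 | 11% | 95.5% |
| 0.30 | 5.86 | 16% | 97.6% |

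Two limits apply. The SD of 7 is stated for the difference in change from pre- to post-training. To the extent that a baseline trait shifts both scores alike, it has already cancelled, which points to the top rows. And the table describes a normal-theory adjusted comparison; the Mann-Whitney test takes no covariates, so its power does not move.

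**4. What they could cost.** An analysis of 100 residents with intercept, arm and TEE observed leaves 97 residual degrees of freedom. Adding pre-test score, semester (linear), diploma and TTE count leaves 93. If all four explained nothing, the variance would rise by roughly 97/93 = 1.04, or about 2% in the standard error. Center is different: 100 residents over 43 centers is 2.3 per center, so fixed center effects would use 42 degrees of freedom. A random effect avoids that.

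**The case against.** The strongest reply has three parts.

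*The baseline tests do no harm.* The variables are summarised as well as compared, and nothing in the text lets a baseline p-value choose a covariate or alter the primary test. This stands. A reader might infer that the plan creates imbalances or adjusts according to which p-values are small. The documents do not support that: the tests only label chance differences. They remain uninformative.

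*A covariate list belongs in an analysis plan that is not shown.* This is partly right, and omitting three variables from a journal article would not be a finding by itself. But the article does fix an adjustment, with a single covariate whose timing is unclear, so improving that stated choice is in scope.

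*The gain is unproven.* This also stands. A reader might take the table to mean that the plan forgoes 3 to 8 points of power on its co-primary outcomes. It does not show that. The R² is assumed, the SD already refers to change, residents who have performed a TEE alone are excluded (which narrows the spread of skill), and the favoured co-primary test is unadjusted. The gain could be close to zero.

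**Conclusion.** The point holds as a minor improvement. The plan tests seven baseline variables at 0.05 between individually randomised arms. The chance of at least one false flag is up to about 30% under independence, and about 23% to 26% under the correlations assumed above. The stated adjustment names one covariate and leaves other collected, plausibly prognostic baseline variables out of every stated model.

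The precision at stake runs from none (R² = 0) to a 16% smaller standard error (R² = 0.30), that is, power of 90% to 98% at the plan's inputs. The low end is more likely once the pre-test is in the model. It concerns the adjusted analysis only. One might infer that the sample size is wrong or the primary comparison biased; neither follows, since the stated 90% power reproduces without any adjustment.

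**What to change.** 1. Report the baseline table by arm, with descriptive statistics and no p-values.
2. State now that the adjusted analysis of each final score includes the pre-test score on the same test, center (the stratification factor, for example as a random effect), residency semester, national echocardiography diploma (yes/no), baseline number of TTE performed and baseline number of TEE observed, whatever the baseline table shows.
3. Say explicitly that the TEE count is the one recorded at baseline. The logbook count after training arises after randomisation and could itself be affected by the training.
4. In the longitudinal mixed model the pre-test is already one of the two outcome measurements, so it should not also be entered there as a covariate.

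The cost is wording and a few degrees of freedom. All the data are already to be collected, and the sample size does not change.

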### Outcomes

The coprimary outcomes of the study to compare the two groups will be the scores in the final theoretical and practical tests after the training will be completed.

The secondary outcomes will be the change in theoretical and practical tests scores from pre- to final-training. In addition, we will assess the satisfaction of participants.

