### Statistical Analysis

#### Sample Size Calculation

Based on recent available literature (13, 15, 19, 21) and considering normalized 0–100 points score ranges for the two co-primary outcomes, a minimally important difference of 5 points (standard deviation 7 points) will be considered for the difference in change from pre- to post-training scores in theoretical and practical tests between the two randomized groups. Under these assumptions, a sample size of 50 subjects per group (for an overall population of 100 participants) will provide 90% power to detect a statistically significant difference between the two groups at a significance level of alpha = 2.5%, applying a Bonferroni correction to account for multiple testing of the two co-primary outcomes.

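### The favoured Mann-Whitney test cannot carry the adjustment that the final analysis requires, and the protocol does not say which analysis decides each co-primary score at 0.025

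*Protocol article*

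**What the plan says.** All places are in the protocol article.

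- **Outcomes.** The co-primary outcomes "will be the scores in the final theoretical and practical tests after the training will be completed". Change is placed lower: "The secondary outcomes will be the change in theoretical and practical tests scores from pre- to final-training".
- **Sample Size Calculation.** The 5-point difference (SD 7 points) is set for "the difference in change from pre- to post-training scores in theoretical and practical tests between the two randomized groups". It is tested at a "significance level of alpha = 2.5%, applying a Bonferroni correction to account for multiple testing of the two co-primary outcomes".
- **Statistical Methods, favoured test.** For the co-primary outcomes, Mann-Whitney tests "will be favored over parametric tests due to the skewed distribution of test scores previously described in the literature".
- **Statistical Methods, longitudinal model.** "Longitudinal analysis of the evolution of the co-primary outcomes over the two time points (pre- and 3-month follow-up) will rely on mixed effects linear regression" modelling.
- **Statistical Methods, adjustment.** Because residents may differ in how many TEE they have observed, "an adjustment for the number of TEE observed will be performed in the final analysis". No model is named for this.
- **Statistical Methods, thresholds.** Two-tailed 0.025 applies to the primary analyses, which are not listed, and 0.05 to every other comparison.

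The number of TEE observed exists in two versions. One is a baseline characteristic (Baseline Participants Characteristics). The other is a logbook count kept after training (Traditional and Simulation-Based Training). The adjustment sentence does not say which is meant.

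**The concern.** A standard Mann-Whitney test compares two groups and takes no covariate. If the final analysis is adjusted, it is not the favoured test. If the favoured test decides, the required adjustment sits somewhere else. The text needs one of these readings and gives neither.

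The mixed model adds a second difficulty. It is parametric, although the same paragraph prefers rank tests because the scores are skewed, and it is attached by name to the co-primary outcomes. Its group-by-time term tests a difference in change, which Outcomes calls secondary but the sample size treats as the co-primary contrast.

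The Bonferroni correction divides alpha between two outcomes only. If the decisive analysis for each outcome is settled after the data are seen, the 5% family-wise rate is no longer assured, and a positive or negative conclusion may depend on which result is put first.

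**Working it through.** **1. The plan's own figure.** Inputs from Sample Size Calculation: difference 5, SD 7, two-sided alpha 0.025, power 90%.

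- Normal approximation: n = 2 × (2.241 + 1.282)² × (7/5)² = 2 × 12.41 × 1.96 = 48.6, so 49 per group.
- Two-sample t-test (noncentral t): 49.93, so 50 per group, with 90.0% power at n = 50.

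The stated 50 per group reproduces. It is a t-test calculation for a mean difference in change. It is not a calculation for a Mann-Whitney test on the final score.

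**2. What each sentence supports as decisive.**

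| Source | Contrast supported | Method |
|---|---|---|
| Outcomes | Final score | not stated |
| Sample Size Calculation | Change | mean difference |
| Statistical Methods, favoured test | Co-primary (final) score | Mann-Whitney, unadjusted |
| Statistical Methods, longitudinal sentence | Evolution of the co-primary outcomes | Linear mixed model |
| Statistical Methods, adjustment sentence | The final analysis | Adjusted, model unnamed |

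The favoured-test and adjustment rows cannot describe the same test. The adjustment may sit inside the mixed model, whose sentence it follows, so the text does not establish three separate analyses.

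**3. Type I error if the choice stays open.** This is a simulation with 50 per group, no true effect, and each test at two-sided 0.025. Assumptions not in the documents: normal scores, complete data, pre/final correlation ρ of 0.3 to 0.7, between-test correlation 0.5, and correlation 0.3 between number of TEE observed and final score. The 7-point SD is taken as the SD of change, so the SD of each score is 7/√(2(1−ρ)), which is 5.9, 7.0 and 9.0 for ρ = 0.3, 0.5 and 0.7. With two time points and complete data, the mixed-model group-by-time contrast equals a t-test on change.

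Probability of at least one significant co-primary result:

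| What may count | Family-wise error |
|---|---|
| Mann-Whitney on the final score only | just under 5% |
| Mann-Whitney or adjusted final score | about 6-7% |
| The change contrast as well | about 8-10% |

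Each test taken alone holds close to 2.5% per outcome. The excess comes only from the freedom to choose.

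**4. Disagreement at the planned 5-point effect, for one score.** At ρ = 0.5, the unadjusted and adjusted final-score tests give different verdicts in about 6% of trials. Mann-Whitney on the final score and the change contrast differ in about 10%, 14% and 33% of trials for ρ = 0.3, 0.5 and 0.7. The second comparison sets two differently ranked outcomes side by side, so it matters only if change is allowed to decide.

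**5. Power of a named alternative.** On the same assumptions, regression of the final score on group, pre-test score and baseline TEE-observed count has power of about 95-99%. Mann-Whitney on the final score has about 66-96%. The regression's type I error is controlled.

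**The case against.** A reader might infer that three planned tests compete for each 0.025 and that the family-wise error is therefore about 10%. The documents do not support that.

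- Outcomes makes change secondary, and Statistical Methods gives non-primary comparisons their own 0.05 threshold. The natural reading is that the final-score comparison takes 0.025 and the mixed model is supportive.
- The adjustment may belong to the mixed model, which would leave two analyses, not three.
- The 8-10% figure needs an analyst to count the change contrast as primary, and the text nowhere permits that outright. All the correlations are assumed, and the simulated scores are not skewed, although skewness is the protocol's reason for rank tests.
- The document is a condensed article. Model details and the labelling of sensitivity analyses are commonly left to an analysis plan, and the article does name an outcome, a favoured test with a reason, and an alpha.

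Most of this stands, and it limits the point. It does not remove it. The problem is a conflict between statements that are present, not missing detail: a favoured test that takes no covariate, an adjustment required in the final analysis, and a mixed model tied by name to the co-primary outcomes. Reading the mixed model as supportive is reasonable, but the sample size section weakens that reading by powering the co-primary comparison on change at the Bonferroni alpha.

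**Conclusion.** The point holds in a limited form. The protocol does not identify the analysis that decides each co-primary score at 0.025, and its favoured test cannot perform the adjustment it requires. The mixed model is most naturally supportive, though the sample size basis leaves room for doubt.

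The cost in error control is modest: about 6-7% in place of a nominal 5% if only the unadjusted and adjusted final-score tests are open, and about 8-10% at most if change may also decide. These rates rest on the assumed correlations, normal scores and complete data given above, and they are illustrative. The textual conflict does not depend on them. The trial is not invalidated, but the wording should be settled before the data are analysed.

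**What to change.** In Statistical Methods, name one decisive analysis per co-primary outcome, tested at two-sided 0.025, that can carry the required adjustment. One suitable choice is a linear regression of the final score on randomised group, with the pre-test score and the baseline TEE-observed count as covariates. Specify that the count is the one collected at randomisation, not the post-training logbook count, which is recorded after allocation and could be affected by it. If skewness is a concern, a rank-based version of the same regression can be used.

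State that the Mann-Whitney test and the longitudinal mixed model are supportive and cannot by themselves establish a co-primary result.

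The cost is one or two sentences. The pre-test score and baseline count are already collected, so no new data are needed. The downside is reliance on a mean-based model for scores that may be skewed; the retained Mann-Whitney test serves as the check on that.

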## Discussion

This study will be the largest multicentre randomized study to assess the impact of simulation-based TEE teaching on the level of skills and practices of residents in cardiology. Simulation-based teaching in cardiology is experiencing a period of significant technological and institutional development. Further, simulation-based teaching has recently became a legal obligation in the evaluation of graduate medical students in France (10).

Previous studies evaluated the difference between TEE simulation training and conventional didactic training and e-learning (11, 12, 14, 20, 21, 23) and only three studies compared simulation training with hands-on training (15, 19, 22) considered as the “gold-standard” for TEE teaching. The majority of these studies showed superiority of TEE simulation training compared to traditional methods (12, 14, 15, 19–23). However, all of these studies were non-randomized (20) or randomized but limited by their sample size and monocentric character. Our multicentric randomized study with stratification by center will reduce the bias of variability in the quality and effectiveness of instructors, which is an essential step in the validation of an educational program. Besides, the majority of studies only evaluated the participants' retention in short-term recall 1 week after TEE education (19), and only a few studies performed long-term recall at 3 months (15). Only two small single-center studies have suggested a benefit of simulation training for residents who played video games with better visual, spatial and motor coordination than other students (15, 24). For that reason, we have chosen to also assess this element in the study.

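### The video-game subgroup analysis is specified only as analyses within strata, and separate within-stratum p-values are not a valid test of whether the training effect differs by gaming history

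*Protocol article*

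**What the plan says.** The protocol article deals with subgroups in one sentence under Statistical Methods: "Prespecified subgroup analyses will be performed after stratifying by prior experience of video games in childhood or currently". The same section sets 0.025 for the primary analyses and "a two-tailed *p* < 0.05 for all other comparisons". It favours Mann-Whitney tests for the co-primary scores. It describes a mixed-effects linear model for how the scores evolve over the two time points, and mentions no video-game term in that model. Nowhere does the article name an interaction test or any other formal comparison of the effects in the two strata.

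The subgroup is defined under Baseline Participants Characteristics as "prior experience of video games in childhood or currently, defined by more than 1 hour per week". The expected share of such residents is not given.

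The reason for the analysis is in the Discussion: "Only two small single-center studies have suggested a benefit of simulation training for residents who played video games". The article says that this is why the factor is being assessed.

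**The concern.** The motive given in the Discussion is that gamers may gain from simulation training, so the natural question is whether the difference between arms depends on gaming history. The procedure in the text is to split the sample and analyse each part. If each part is then judged by its own p-value, one stratum may reach significance and the other not, simply because each holds only part of the sample. That pattern can arise when the effect is identical in both strata.

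What is at stake is a secondary message of the trial. A reader could conclude that simulation helps only residents with, or only residents without, gaming experience, and that could influence who is offered the training. The co-primary comparison is not touched.

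**Working it through.** **Inputs from the Sample Size Calculation and Statistical Methods sections.** Effect and SD: "a minimally important difference of 5 points (standard deviation 7 points". Size: "a sample size of 50 subjects per group (for an overall population of 100 participants". Primary threshold: "at a significance level of alpha = 2.5%, applying a Bonferroni correction to account for multiple testing of the two co-primary outcomes". Threshold for the subgroup analyses: "0.05 for all other comparisons". The plan states the 5 points and SD 7 for the difference in change scores; I use them as given.

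**Assumptions.** The share of gamers is varied because the plan gives none. The arms are taken as balanced within strata, although randomization is stratified by center only. The true effect is the same in both strata.

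**1. Reproduce the plan's figure.** n per group = 2(z₀.₉₈₇₅ + z₀.₉₀)² × (7/5)² = 2 × (2.241 + 1.282)² × 1.96 ≈ 48.6, so 49 against the stated 50. Power at 50 per group is 90.8% by normal approximation and 90.0% by noncentral t. The plan's figure holds.

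**2. Power within strata and discordance, N = 100.** Power p₁ and p₂ come from the two-sample noncentral t at two-sided 0.05, with a 5-point effect and SD 7. The strata contain different residents, so their tests are independent and P(exactly one significant) = p₁(1 − p₂) + p₂(1 − p₁).

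| Split | Per arm in each stratum | Power | Exactly one significant |
|---|---|---|---|
| 50/50 | 25 and 25 | 0.697, 0.697 | 2 × 0.697 × 0.303 ≈ 0.42 |
| 60/40 | 30 and 20 | 0.776, 0.595 | 0.776 × 0.405 + 0.595 × 0.224 ≈ 0.45 |
| 70/30 | 35 and 15 | 0.838, 0.472 | 0.838 × 0.528 + 0.472 × 0.162 ≈ 0.52 |
| 80/20 | 40 and 10 | 0.884, 0.327 | 0.884 × 0.673 + 0.327 × 0.116 ≈ 0.63 |

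These rates are per outcome, and there are two co-primary scores. Mann-Whitney tests in 10,000 simulated trials gave 44% at 50/50 and 53% at 70/30, so the result does not depend on using the t-test.

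**3. Sensitivity to effect and sample size.**

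- N = 100, even split: 36% for a 2.5-point effect, 12% for 7 points, below 1% for 10 points.
- N = 200, 5-point effect: 11% at 50/50, 23% at 70/30, 41% at 80/20.
- N = 200, 2.5-point effect, even split: 49%. A larger sample lowers the rate only if the effect is large enough for both strata to be well powered.

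**4. The interaction test.** The standard error of the difference between stratum effects is 7√(2/g₁ + 2/g₂), where g₁ and g₂ are the numbers per arm in each stratum.

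- At an even split this is 7√(2/25 + 2/25) = 2.80 points.
- Power for a 5-point difference in effects is Φ(5/2.80 − 1.96) = Φ(−0.17) ≈ 43%. It is 37% at 70/30 and 30% at 80/20.
- The difference detectable with 80% power at an even split is 2.80 × (1.960 + 0.842) ≈ 7.8 points. It is 8.6 points at 70/30 and 9.8 at 80/20.
- With one common 5-point effect, the interaction test was falsely significant in 5.2% (50/50) and 5.0% (70/30) of the simulated trials, close to its nominal 5%.

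**The case against.** The strongest reply is that the text is one sentence in a condensed article. It names the stratifying variable. It does not say that discordant p-values will be read as a differential effect, and the general 0.05 rule would cover an interaction test equally well. The full protocol or an analysis plan may add one. This is fair, and it limits the point to the method as published. But the article does fix an approach for a prespecified analysis, and that approach stops short of the comparison its stated motive calls for.

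The motive is also partly inferred. Baseline Participants Characteristics gives a second reason for collecting gaming history, its association with performance on simulation-based models, which is prognostic. Neither the study hypothesis nor the Outcomes section mentions video games. Effect modification is the natural reading of the Discussion, but it is not a formally stated hypothesis.

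A reader might go further in two ways that the document does not support:

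- **That the trial will probably report a benefit in one stratum only.** At the even and 60/40 splits discordance is below one half. It passes one half only at more uneven splits, which are assumptions. The plan covers more than 70% of French cardiology residents and treats 100 as a requirement, so recruitment may exceed it, and the true effect may exceed the minimally important difference. Both lower the 42% sharply. Reporting a differential benefit would also take an interpretive step that the plan does not state.
- **That stratified analyses can reveal nothing about effect modification.** Stratum estimates with confidence intervals let the two effects be compared. What is invalid is an inference from separate p-values.

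**Conclusion.** The concern holds in a limited form. As published, the subgroup analysis consists of analyses within strata, without a formal comparison between them, while its motive is most naturally a question about a difference in effects. If within-stratum p-values are used to answer it, the risk of a false contrast under the plan's own N, effect and SD is about 42% to 52% per outcome for splits from 50/50 to 70/30, against a nominal 5% for an interaction test. The size rests on the assumed share of gamers, a sample near 100, and a true effect near 5 points in both strata. The primary analysis, sample size and conduct are unaffected. This is an inexpensive improvement to a secondary analysis.

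**What to change.** Replace the subgroup sentence with a specification that does the following:

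- For each co-primary score, fit a linear regression, or the mixed model already planned, with an arm-by-video-game interaction. In the mixed model the relevant term is the one for the arm difference at the final test or in change. The favoured Mann-Whitney test carries no interaction term, so one of these models has to be named. Robust or bootstrap standard errors would answer the plan's concern about skewed scores.
- Report the difference between stratum effects with its confidence interval, and each stratum's effect with its own interval.
- State that no subgroup claim will rest on within-stratum p-values.
- Label the analysis exploratory and state its low power: about 43% for a 5-point difference in effects at N = 100 and an even split, and less if the split is uneven.

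The cost is a few sentences and one modelling choice. No new data are needed, because gaming history is already collected at baseline. The price is that the analysis will probably be inconclusive unless the difference between strata is large, roughly 8 points or more at this sample size.
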